**Figure 2 fig2:**
[figure not shown]
The BRAID model aligns closely with the IAP2 spectrum of public participation (29, 30).

BRAID is adoptable to a wide range of public health issues and has the potential to navigate the ever-changing needs of the communities that surround health systems (15). Previously implemented by the team to elicit community perceptions and hesitations related to the COVID-19 vaccine, BRAID was successful in achieving robust community engagement and building trust (20).

Our procedures for this BRAID mixed-methods study were adapted from the Community Engagement Studios Manual developed by Vanderbilt’s and Meharry’s Clinical and Translational Science Award community engagement core (21). Figure 3 outlines how our study design aligns with the biphasic BRAID model. Each of the panels in the figures are described in detail in the proceeding sections:

**Figure 3 fig3:**
[figure not shown]
BRAID study design.

### BRAID phase 1: knowledge and trust building and health message codesign (steps 1–2)

2.2

#### Identifying trusted community messengers (step 1)

2.2.1

We will first partner with local community-based organizations (CBOs) to identify and engage trusted community messengers (“Community Experts”), well-connected and influential individuals from target communities who represent the communities’ voice. In the BRAID model, CBOs able to identify and help recruit trusted messengers are called “BRAID Strands.” Natural BRAID Strands for this effort include but are not limited to faith-based groups, senior centers, schools, tenants’ councils, libraries, museums and cultural institutions, federally qualified health centers, clinics, therapy groups and food assistance programs. These organizations are pillars of the community, with their members typically having robust social networks. This makes them ideal candidates for the BRAID trusted messenger role. We will compensate our partnering BRAID Strands for performing administrative tasks as outlined in Appendix B. Aligned with the best practices of community-based participatory research (CBPR), individual Community Experts will be compensated for their participation in Conversation Circles. Compensation will reflect the standards established by PCORI-funded research guidelines (22).

#### BRAID Conversation Circles (step 2)

2.2.2

Once trusted messengers are identified, we will invite them to participate in a series of dynamic BRAID “Conversation Circles.” During these dialogues, a motivational interviewing (MI) aligned facilitation style will be employed to elicit important community perspectives, understand “*what matters*” most to the community, and create a space where clinical and scientific experts are invited to share accurate information that addresses community concerns (23). We envision that themes related to trust in research, science, healthcare, structural racism, and health disparities will emerge, and that gaps in knowledge and misinformation will be identified. Further, Conversation Circles will be similarly used to obtain community feedback and sentiment on published research findings directly relevant to members in their community. Throughout the Conversation Circle process, a facilitator will guide the participants towards critically reviewing learned information and codesigning solutions and accurate messages that they deem appropriate to share with their community networks.

We will implement up to 15 unique Conversation Circle cohorts. Four to 12 trusted community messengers will participate in each cohort, and clinical and scientistic guests will be selected and invited to attend and contribute to the dialogue based on their ability to address emerging community concerns. Each Conversation Circle will meet 1–5 times with 1–3 weeks between each circle. Conversation Circles will take place in-person or virtually using Zoom and will be recorded and transcribed. Surveys will be collected before and after each Conversation Circle to understand participant experience and confidence in knowledge of accurate information, assess participant perception of the information shared (i.e., the benefit of having diversity in clinical trials, protections in place to protect study participants, relevant study findings), and explore participant desire and self-efficacy to share accurate information downstream to their community (Appendix C).

### BRAID phase 2: information dissemination (BRAIDing; step 3–4)

2.3

#### Getting ready to BRAID: motivational interviewing training (step 3)

2.3.1

We anticipate that teaching BRAIDers Motivational Interviewing (MI) based communication skills will strengthen their confidence and comfort in sharing co-created educational messages that may be controversially perceived by their community (i.e., vaccine and clinical trial messages). Participants will therefore be invited to participate in a 60–90 min “Getting Ready to BRAID” session which will introduce MI spirit and skills including reflective listening, and the ASK-TELL-ASK tool for sharing information and advice. The curriculum will be tailored to incorporate guidance on how to respond to the specific types of resistance statements that Community Experts encounter.

#### Assessing readiness to BRAID: exit interviews (step 4)

2.3.2

Following the “Getting Ready to BRAID” session, a structured interview with each BRAIDer will be conducted to assess their BRAIDing comfort and intention. BRAIDers will be asked a series of questions that align with the PROSCI™ Change Management ADKAR (Awareness, Desire, Knowledge, Ability and Reinforcement) model, and their responses will be recorded on a scale from 1–5 (1 = “Not At All,” 5 = “Extremely”; Appendix D) (24). Interview answers will be collected in a SurveyMonkey form by the research assistant. These responses will be used to identify factors influencing BRAIDers’ readiness for sharing information throughout their social networks, and for responding to individuals’ needs for further training and resources to improve their readiness.

To assess BRAIDers experience and effectiveness in sharing information, we will also conduct a network analysis beginning in the first exit interview. This will involve first asking each BRAIDer to identify up to 8 individuals (e.g., family, friends, coworkers) with whom they intend to share the co-created messages. For each of these individuals, we will collect their initials, demographic information, relationship to the BRAIDer, and the BRAIDer’s prediction of the individual’s anticipated reaction to the messages. BRAIDers will be provided with materials introduced during the Conversation Circles, including FAQs, websites, and videos, presented in formats that are easily shareable with others. After 3–6 weeks, each BRAIDer will complete a second exit interview to discuss their experience sharing information and provide feedback on how their chosen community members responded to the messages shared.

#### Tracking BRAIDer message dissemination through social media (step 5)

2.3.3

In addition to the structured interviews, for our network analysis we will also monitor BRAIDer message dissemination through social media. Codesigned messages, video links, and other clinical trials materials and resources will first be posted on a dedicated BRAID website. In order to monitor engagement all website links will feature Google analytics campaign tracking. When a link is copied and shared by a BRAIDer, their unique alpha-numeric campaign code (which will not include identifying information) will be appended to the resource’s URL. This will enable us to monitor which BRAIDers are responsible for a given share of website traffic.

### Post BRAID: focus group (step 6)

2.4

After BRAIDers personally gain BRAIDing experience, they will be invited to participate in a focus group designed to understand BRAIDers experience sharing information, whether they felt that learning MI skills was valuable, and if they utilized these skills during the BRAIDing process. The insights gathered from these focus groups will support the opportunity to collaborate and co-design acceptable health messages with community experts, reflecting *what matters* most to them.

### Data analysis plan

2.5

BRAID is a mixed-methods study. Key quotes and themes from the transcriptions of the audio or video-recorded Conversation Circles will be identified via inductive thematic analysis based on a codebook that will be developed by the BRAID research team. At least 2 BRAID research team members will independently code each Conversation Circle transcript using Dedoose qualitative analytics software. Following initial Conversation Circle transcript coding, the BRAID team will collectively assess inter-coder reliability and alignment of transcript coding to the established code book categories. Network analysis will be conducted using data collected from the “Getting Ready to BRAID” interview responses to identify associations between BRAIDer responses and successful BRAIDing. Descriptive statistics and quantitative data from both pre- and post-Conversation Circle survey responses will be analyzed using SPSS and/or R. All data will be analyzed using grounded theory methods (25, 26). Google campaign analytics will be used to track the reach of each BRAIDer’s message dissemination through social media.

## Discussion

3

For members of historically underrepresented communities, fostering trust in research and science is vital to increasing their participation in research projects. By respecting the community voice through engagement with trusted messengers and incorporating codesign principles, BRAID may be able to foster community trust among members who might otherwise be difficult to reach. In fact, the BRAID model has already been shown to foster rich dialogue regarding COVID-19 vaccine hesitancy in the Bronx, and has also demonstrated its ability to empower trusted messengers (BRAIDers) to share accurate information about vaccine safety (20).

We anticipate that the BRAID model could be rapidly implemented with the help of diverse community partnerships to identify health disparities that exist across socioeconomic status, age, geography, gender, disability status, sexual identity and orientation, citizenship status, and more. Furthermore, as a community engagement model, BRAID can be readily adapted to extend beyond increasing clinical research participation. We envision that the model could potentially be used to build trust, co-design and disseminate accurate health messages, and obtain community feedback on health and social care issues that drive health disparities including, but not limited to, vaccination status, food insecurity, mental healthcare, and cancer prevention.

Our study has several limitations. First, recruitment bias may be introduced because our CBO partners will be responsible for identifying potential Community Experts rather than community members volunteering themselves or being selecting by the BRAID research team. We attempted to minimize this bias by creating clear guiding principles for objectively identifying BRAID participants which will be shared with our CBO partners and included in our BRAID manual. Our protocol is also potentially subjective to social desirability bias. While it is important to recognize that the goal of BRAID Conversation Circles is to provide a space for bidirectional dialogues that may influence or altogether change the attitudes and beliefs of participants, we will distribute pre- and post-surveys outside of the Conversation Circle group setting to minimize this risk. As the process of engaging with participants who do not complete their series of Conversation Circles is not included in the current protocol, potential for attrition bias also exists. Lastly, we acknowledge that our study findings may not be clearly generalizable to communities different than the ones included within the Conversation Circles. Nevertheless, the BRAID model can be adapted to address a broad range of public health concerns regardless of community demographics.

BRAID has the potential to serve as a foundational infrastructure for a Learning Health Care Community (27, 28). In this paradigm, a robust network of “BRAIDers” who trust science and the healthcare system, could be leveraged by an anchor institution to provide ongoing local community input into health equity programming, research design, and dissemination. This kind of long-term investment can further cultivate meaningful community partnerships and collaborations that address the underlying structural factors that drive health disparities, in order to achieve health equity.

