## Abstract

Cultural beliefs, personal experiences, and historic abuses within the healthcare system—rooted in structural racism—all contribute to community distrust in science and medicine. This lack of trust, particularly within underserved communities, contributes to decreased participation in clinical trials and a lack of representation in the data. Open dialogue about community concerns and experiences related to research participation and medical care processes can help build trust and change attitudes and behaviors that affect community health. This protocol outlines an approach to increase trust in science and clinical trials among communities in the Bronx, New York that are typically underrepresented in research data. Bridging Research, Accurate Information and Dialogue (BRAID) is a two-phased, evidence-based community engagement model that creates safe spaces for bilateral dialogues between trusted community messengers, and clinicians and scientists. The team will conduct a series of BRAID Conversation Circles on the topic of clinical trials with local trusted community messengers. Participants will be members of the community who are perceived as “trusted messengers” and can represent the community’s voice because they have insight into “what matters” locally. Conversation Circles will be audiotaped, transcribed, and analyzed to identify emergent challenges and opportunities surrounding clinical trial participation. These key themes will subsequently inform the codesign and co-creation of tailored messages and outreach efforts that community participants can disseminate downstream to their social networks. Surveys will be administered to all participants before and after each Conversation Circle to understand participants experience and evaluate changes in knowledge and attitudes about clinical trials, including protections for research participants the advantages of having diverse representation. Changes in motivation and readiness to share accurate clinical trial information downstream will also be assessed. Lastly, we will measure participants dissemination of codesigned science messages through their social networks by tracking participant specific resource URLs of materials and videos posted on a BRAID website. This protocol will assess the effectiveness and adoptability of an innovative CBPR model that can be applied to a wide range of public health issues and has the potential to navigate the ever-changing needs of the communities that surround health systems.

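### Attrition is acknowledged but given no countermeasure, so change over a series rests on those who stay; and the focus group on the MI training, as worded, misses trained people who never shared

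*Protocol article*

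**What the plan says.** **Surveys.** The Abstract states: "Surveys will be administered to all participants before and after each Conversation Circle". Section 2.2.2 (BRAID Conversation Circles) repeats this and sets the schedule: "Each Conversation Circle will meet 1–5 times with 1–3 weeks between each circle".

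**Attrition.** The limitations paragraph of the Discussion says that "the process of engaging with participants who do not complete their series of Conversation Circles is not included in the current protocol", and so "potential for attrition bias also exists". The same paragraph answers recruitment bias with guiding principles for the community organisations, and social desirability bias with surveys given outside the group. No such step follows for attrition.

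**Training.** Section 2.3.1: "Participants will therefore be invited to participate in a 60–90 min" training session. Attendance is therefore voluntary.

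**Interviews and reach.** Section 2.3.2 gives each BRAIDer an interview after training and another 3–6 weeks later. Section 2.3.3 attributes website traffic to BRAIDers through individual campaign codes. Neither makes having shared a condition.

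**Focus group.** Section 2.4: "After BRAIDers personally gain BRAIDing experience, they will be invited to participate in a focus group". Among other things it asks "whether they felt that learning MI skills was valuable, and if they utilized these skills during the BRAIDing process".

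**The concern.** The study is about distrust. Those who distrust the process most, or who find the messages hardest to pass on, are plausible early leavers and plausible non-sharers. If they drop out of the data as the study proceeds, the results lean towards people for whom the model worked.

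Two quantities are exposed:

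- **Change in knowledge and attitudes over a whole series.** A last survey exists only for those who attended the last circle.
- **Perceived value of the MI training.** Section 2.3.1 predicts that training will strengthen confidence and comfort in sharing. Someone who trained and then shared with nobody is the most informative case against that prediction, and is the person whom the focus-group invitation appears to leave out.

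The Abstract says that the protocol will assess the model's effectiveness and adoptability, so both quantities bear on its stated aim.

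**Working it through.** The article states no dropout rate, sample size or effect size, so there is no figure of its own to reproduce. The check is of the text first, then of what the bias could amount to under stated assumptions.

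**1. Who contributes change data.**
- Surveys precede and follow each circle. A person who leaves after circle *k* of *m* has up to *k* pre/post pairs and no stated later survey.
- In a one-meeting cohort (*m* = 1) there is no later circle to miss, and this mechanism does not arise.
- In a five-meeting cohort there are four gaps of 1–3 weeks, so the series spans 4 × 1 = 4 to 4 × 3 = 12 weeks. A person who leaves after circle 2 gives two pairs where a completer gives five. Pooling all pairs with equal weight therefore gives more weight to those who stay.

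**2. Scale.** Section 2.2.2 says: "We will implement up to 15 unique Conversation Circle cohorts", with 4 to 12 people in each. At the full 15, enrolment is 15 × 4 = 60 to 15 × 12 = 180.

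**3. Possible overstatement of first-to-last change.** Let *d* be the proportion who leave and *r* the leavers' mean change as a fraction of the completers'. The ratio of the completers-only mean to the all-participant mean is 1 / [(1 − *d*) + *r d*]. Both *d* and *r* are assumptions.

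| Assumed dropout *d* | Completers of 60 / 180 | Ratio, *r* = 0.5 | Ratio, *r* = 0 |
|---|---|---|---|
| 10% | 54 / 162 | 1/0.95 = 1.05 | 1/0.90 = 1.11 |
| 20% | 48 / 144 | 1/0.90 = 1.11 | 1/0.80 = 1.25 |
| 30% | 42 / 126 | 1/0.85 = 1.18 | 1/0.70 = 1.43 |
| 40% | 36 / 108 | 1/0.80 = 1.25 | 1/0.60 = 1.67 |

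This applies only if a first-to-last comparison is made among completers. It does not apply to the pre/post change within a single circle.

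**4. Focus group.** Suppose that 80% of members call the MI training valuable and that a fraction *f* of trained people have shared. With nothing known about the rest, the share among all trained lies between 0.8*f* and 0.8*f* + (1 − *f*):
- *f* = 0.9: 72% to 82%
- *f* = 0.7: 56% to 86%
- *f* = 0.5: 40% to 90%

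The 80% and the values of *f* are assumptions. The bounds show how much is left unknown, not a direction.

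**5. Reach.** A campaign code with no traffic is visible as zero, and the second interview can record that nobody was told. So a BRAIDer who did not share can be seen. Selection acts earlier: a person who left the circles or declined training may never become a BRAIDer, and the article does not say whether someone who left could still be trained. The term is also used in two ways. Section 2.1 defines BRAIDers as messengers who share, whereas section 2.3.2 applies it to people who so far only intend to.

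**The case against.** The strongest reply is that the authors disclose the limitation themselves, that surveys go to all participants around every circle, and that no completers-only analysis is stated. Leavers therefore do contribute data, and the larger figures above need both an analysis that the article does not specify and the extreme case of no change in leavers. This stands, and it limits the point to cumulative change and later circles. It does not remove it: disclosure is not a countermeasure, and the article says positively that the process is outside the current protocol, so this is not a detail lost in condensing.

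A second reply is that the focus group is qualitative, that questions about using skills while sharing need sharing experience, and that section 2.4 says when BRAIDers are invited without saying that others are excluded. The exclusion is indeed inferred from that timing, though it is the natural reading. The post-training interview in section 2.3.2 does cover comfort and intention, but the question of MI value is stated only in section 2.4, and people who never shared can answer it.

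A reader might go further and infer that change, reach and training value are all estimated in a self-selected group of successes, or that leavers get no further contact of any kind. The documents do not support this. Change is surveyed at every circle attended, and zero reach is observable among BRAIDers. The Discussion says that a process of engaging non-completers is not included, not that contact ends. Nor is a proportion sharing among trained people biased for trained people; the proportion among all enrolled is a different quantity.

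Finally, the choice of model and of sensitivity analyses belongs to an analysis plan that is not shown, and its absence here is not a fault.

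**Conclusion.** The concern holds in a limited form.

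- **Attrition** is named and, unlike the two other biases that the Discussion tries to reduce, left without a remedy. In multi-meeting cohorts, change over the series and data from later circles rest on those who stay.
- **The focus group**, read naturally, leaves out trained people who shared with nobody, so its view of MI value leans towards those who did share.
- **Reach** among BRAIDers is not restricted in this way, but its denominator may omit people lost before training.

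The size is unknown. The range of 5–25% (leavers change half as much) or 11–67% (leavers do not change) rests on assumed dropout of 10–40% and on a completers-only first-to-last comparison. An upward direction assumes that leavers change less than completers. That is plausible in a study of distrust, but the documents do not show it.

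**What to change.** 1. Send the final post-survey to everyone who completed a first pre-survey, whether or not they finished the series. Surveys are already given outside the group, so the route exists.
2. Include everyone with at least one survey in the analysis of change, and compare first-survey scores of leavers and completers.
3. Report the numbers enrolled, completed, trained and shared. Show dissemination over all enrolled Community Experts as well as over BRAIDers, label these as two different quantities, and use the term BRAIDer in one sense.
4. Invite everyone who attended the MI training to the focus group, and say explicitly that this includes those who did not share.

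The cost is a few extra survey and focus-group contacts. The reported results may turn out less favourable.
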